## Abstract

**Background:**

Mild cognitive impairment (MCI) associated with diabetes mellitus (DM) is common among older adults, and self-management is critical to controlling disease progression. However, both MCI and DM are heterogeneous diseases, and existing integrated self-management interventions do not consider patient differences. Grouping patients by disease characteristics could help to individualize disease management and improve the use of available resources. The current study sought to explore the feasibility and effectiveness of a stratified support model for DM-MCI patients.

**Methods:**

Eighty-four DM-MCI patients will be randomly divided into an intervention group and a control group in a 1:1 ratio. The intervention group will receive a self-management intervention using the stratified support pattern-based internet-assisted therapy (SISMT), while the control group will receive the health manual intervention (HMI). The study recruiter will be blinded to the group allocation and unable to foresee which group the next participant will be assigned to. At the same time, the allocation will be also hidden from the research evaluators and participants. After 12 weeks and 24 weeks, cognitive function, blood glucose, self-management ability, psychological status, health literacy, and self-management behavior of patients in both groups will be measured and compared.

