### Sample size calculation

The required sample size is estimated using PASS v11.0 (NCSS, Kaysville, UT, USA) based on a completely random design for comparing the means of two independent samples. To our knowledge, there is no previous study on a stratified support pattern-based internet-assisted self-management therapy for DM-MCI in mainland China, so we estimate the effect size of one of the outcomes (HbA1c) based on previous research on patients with DM-MCI [42]. This study find that HbA1c scores in intervention and control group are 6.49 ± 1.59 and 6.97 ± 0.73, respectively. A sample size of 34 participants per group was determined to be sufficient to detect an effect with a type 1 error rate of 5% (α = 0.05) and 90% power (β = 0.1). A total of 68 participants will be needed, with 34 participants per group. Considering a 20% loss of follow-up rate, the final sample size is 86, with 43 participants per group.

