### Randomization, blinding, and concealed allocation

Ensuring allocation concealment, participants will be randomized (after obtaining written informed consent, eligibility screening, and baseline assessment) to the intervention and control groups at a 1:1 ratio by a study staff member (who will not be involved in participant recruitment or outcome assessment) using Research Randomizer software (http://www.randomizer.org/). Participants in the intervention group will be assigned to different categories of the intervention group based on their cognitive function and self-management characteristics and will receive Intervention measures with different frequencies. Participants in the control group will be assigned to different categories of the control group based on their cognitive function and self-management characteristics, too, but there is no difference in intervention frequency. The participants will then be told their group assignment by the intervention staff. Due to the nature of non-pharmacological interventions, only the outcome assessors and data analysts (not the participants or intervention staff) will be blinded to group allocation.

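### The abstract says 84 patients will be randomised and the sample-size section says 86; only 86 follows from the plan's own 34 per group and 20% loss

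*Protocol article*

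**What the plan says.** The abstract of the protocol article, under Methods, states: "Eighty-four DM-MCI patients will be randomly divided into an intervention group and a control group in a 1:1 ratio". At equal allocation that is 42 per group.

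The section Sample size calculation sets the number in two steps. First: "A total of 68 participants will be needed, with 34 participants per group". Then: "Considering a 20% loss of follow-up rate, the final sample size is 86, with 43 participants per group".

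The section Randomization, blinding, and concealed allocation confirms that participants are assigned "to the intervention and control groups at a 1:1 ratio", so the total must be an even number if the groups are to be equal. It gives no total of its own.

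**The concern.** Both figures describe the number to be randomised. The 84 cannot be the number left after loss to follow-up, because the sample-size section puts that at 68. Both are current text, so this is not a trace of an amendment.

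The randomisation total is the benchmark against which the final report's enrolment will be judged. With two values in print, 84 randomised could be read as full enrolment or as a shortfall of two, and 86 as full enrolment or as two too many. The abstract is the part most readers see, and it carries the figure that does not follow from the calculation.

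**Working it through.** **Inputs**

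- Number required after loss: 34 per group, 68 in total (Sample size calculation).
- Loss to follow-up: 20% (same section).
- Allocation: 1:1 (abstract; Randomization, blinding, and concealed allocation).
- Totals to compare: 86 (Sample size calculation) and 84 (abstract).

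**Step 1. Reproduce the plan's figure.** Number to randomise per group = required number / (1 − loss) = 34 / (1 − 0.20) = 42.5, rounded up to 43. Total = 2 × 43 = 86. This matches the sample-size section exactly.

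**Step 2. Look for a route to 84.**

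| Method | Calculation | Total |
|---|---|---|
| Divide per group, round up | 34/0.8 = 42.5 → 43 | 86 |
| Divide the total | 68/0.8 = 85 | 85 (86 for equal groups) |
| Multiply per group, round up | 34 × 1.2 = 40.8 → 41 | 82 |
| Multiply the total, round up | 68 × 1.2 = 81.6 → 82 | 82 |
| Divide per group, round down | 34/0.8 = 42.5 → 42 | 84 |

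Of these, only rounding 42.5 down gives 84, and rounding down leaves fewer patients than the rule requires.

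**Step 3. Check each total against the requirement at 20% loss.**

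- 84: 42 × 0.8 = 33.6 per group; 84 × 0.8 = 67.2 in total. Required: 34 and 68. Expected shortfall: 68 − 67.2 = 0.8 patients in total.
- 86: 43 × 0.8 = 34.4 per group; 86 × 0.8 = 68.8 in total. The requirement is met.

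**Step 4. Loss each total can absorb while keeping 34 per group.**

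- 42 per group: 1 − 34/42 = 0.190, or 19.0%.
- 43 per group: 1 − 34/43 = 0.209, or 20.9%.

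The stated 20% lies between the two, so 43 per group can absorb it and 42 cannot.

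**Step 5. What this check does not cover.** The steps above take 34 per group as given. The section bases that number on this: "HbA1c scores in intervention and control group are 6.49 ± 1.59 and 6.97 ± 0.73". The difference is 6.97 − 6.49 = 0.48 and the pooled SD is √((1.59² + 0.73²)/2) = 1.237, so the standardised difference is 0.48/1.237 = 0.388. At that effect, two-sided α of 0.05 and a normal approximation, 34 per group gives about 36% power, and 90% power would need 140 per group. If the test is one-sided (the article does not say), the figures are about 48% and 114 per group. Agreement between the two totals therefore says nothing about whether 34 is enough.

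**The case against.** The strongest reply is that the sample-size section settles the matter. It is where the size is set, it shows the derivation, it calls 86 final and it gives the number per group. The abstract line is a one-sentence summary with no derivation, most likely a slip or 42.5 rounded down. On this view a careful reader knows that 86 governs, the difference is two participants, and no analysis or conclusion changes. Most of this stands, and it is why the point is a minor consistency correction. It does not remove the conflict: the article nowhere says which total governs, and the abstract is wrong against its own Methods.

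Four stronger readings are tempting, and the document does not support them.

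- *That the trial will stop recruiting at 84.* Nothing says so. The shortfall in Step 3 arises only if 84 is the working target.
- *That 84 leaves 33 per group, two patients short.* Rounding both groups down overstates it. The expectation is 67.2 in total, about 34 in one group and 33 in the other, or about one patient short. The 20% is itself a round planning assumption.
- *That power falls from 90% to about 89%.* That comparison needs a standardised effect of about 0.80, obtained by working backwards from 34 per group and 90% power. The section's HbA1c figures give about 0.39, so these percentages do not describe this trial.
- *That moving to 86 secures the planned power.* It only makes the abstract agree with the sample-size section.

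**Conclusion.** The point holds as an inconsistency between two parts of the article. The abstract's 84 and the sample-size section's 86 cannot both be the number to be randomised, and only 86 follows from 34 per group with 20% loss. The inflation step in the sample-size section is correct; the figure out of line is the one in the abstract.

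The size is small: two participants randomised and, if 84 were used, about one evaluable patient in total below the stated 68. This rests on three assumptions: the 20% applies to both groups alike, 34 per group is the number wanted after loss, and the groups are equal. The document states or plainly implies all three. The conclusion does not depend on the effect size or on whether the test is one- or two-sided. It gives no support to the claim of 90% power, which has to be examined separately.

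**What to change.** Change the abstract to read: Eighty-six DM-MCI patients (43 per group). One total then holds throughout. This costs one number in the text, and no participants beyond those the sample-size section already plans for.

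If 84 is the real target, leave the abstract and change Sample size calculation to 42 per group. Then restate **one** of the following, not both:

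- the expected evaluable number at 20% loss: 33.6 per group, about 67 in total; or
- the loss that still keeps 34 per group: 19%.

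These are alternatives. At 19% loss, 42 per group still yields 34 (42 × 0.81 = 34.02), so printing a reduced evaluable number beside a reduced loss would create a new contradiction.

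If the evaluable number is later revised for other reasons, update the abstract and the sample-size section together.

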**Discussion:**

This study developed a stratified support pattern-based internet-assisted to provide self-management intervention for patients with DM-MCI. The impact of different models and forms of self-management intervention on cognitive function, blood glucose management, and psychological status health literacy and self-management behavior of patients will be assessed. The results of this study will inform related intervention research on the stratified support pattern-based internet-assisted self-management therapy, and help to slow the decline of cognitive function in patients with DM-MCI.

**Trial registration:**

ChiCTR2200061991. Registered 16 July 2022.

## Background

Diabetes mellitus (DM) is one of the chronic diseases that develop rapidly and threaten global health. According to the data of the International Diabetes Federation (IDF) in 2021, about 537 million adults (20–79 years old) worldwide suffer from diabetes, which will rise to 783 million by 2045. During this period, the world population is estimated to increase by 20%, while the number of patients with diabetes is estimated to increase by 46% [1]. It can be seen that the form of diabetes is not optimistic. DM is characterized by persistent hyperglycemia, which will not only cause chronic damage to blood vessels, brain and other tissues and organs [2, 3], but also affect the nervous system function of patients, thus causing cognitive impairment [4]. Some studies have further proved the correlation between this disease and found that most diabetes patients will have cognitive impairment, and 25–36% of them have mild cognitive impairment (MCI) [5]. Some research teams have called this type of patient as DM-MCI [6–8], and one of research teams conducted a survey on the prevalence of this type of patient. It was found that the overall prevalence of DM-MCI is 45%, indicating that DM-MCI is affecting residents on a large scale [8].

MCI refers to a stage in which a patient's cognitive function has been impaired, but its severity is not sufficient to constitute dementia, and it is a precursor to the development of dementia [9]. According to statistics, the global prevalence of elderly MCI is approximately 3–22%, with approximately 5–10% of these patients developing dementia annually [10, 11]. As one of the risk factors for cognitive impairment, diabetes not only increases the risk of cognitive impairment, but also accelerates the disease progression of MCI. Fortunately, mild cognitive function has a characteristic of bidirectional transformation. It means that MCI is an intervention stage in disease progression [12]. And a study has found that MCI patients' self-management ability related to blood glucose control is poor, which will affect the blood glucose control of patients. This undoubtedly further accelerated the progress of cognitive impairment in patients with DM-MCI [13]. Therefore, improving self-management ability has become an important measure to prevent the deterioration of disease in patients with DM-MCI.

Self-management is a dynamic and continuous self-regulation process that utilizes patients' own skills and knowledge input to effectively control their life confidence and motivation, leading to behavioral changes. It is an important method for controlling and slowing down the progression of chronic diseases, thereby affecting patients' psychological state, quality of life, and happiness [14]. While strong self-management can delay disease deterioration, poor self-management can increase disease progression [15]. Prior studies on the self-management of patients with DM and/or MCI have achieved positive results. In a study by Katja et al., patients with type 2 diabetes used telemedicine-assisted self-management behavior over a 3-month period [16]. The intervention included diet, physical activity, blood glucose monitoring, first aid training, and clinical and stress management, and telephone guidance was conducted based on each patient’s personal needs. Glycated hemoglobin levels and self-management behavior scores improved significantly in response to the intervention. Yang Q et al. developed self-management measures based on a forgetting pattern of the human brain towards new things to provide intervention to patients with MCI [17]. After 3 months, there were improvements in the cognitive function and daily living ability of the patients. However, the intervention for DM-MCI patients are mostly single content, such as cognitive training or diet only for patients [18, 19]. Few studies have focused on comprehensive self-management interventions that are individualized and do not use an integrated intervention mode.

MCI and DM are heterogeneous diseases, and this heterogeneity increases when the conditions co-occur in the same individual [20, 21]. Personalized intervention is an important way to address this issue [22]. However, in populous countries like China [23], it can be difficult to implement targeted intervention measures. In addition, personalized medicine requires many human resources, making it a challenge to sustain it over a long time period. To address this, relatively individualized, or “stratified” intervention measures, were developed. The meaning of “stratified” intervention is to classify patients based on their characteristics of diseases, and provide corresponding intervention for various categories of patients. Many studies have adopted such “stratified” intervention. Li et al. used applied acute physiology and chronic health evaluation II (APACHE II) to evaluate the illness severity and self-care ability of hemodialysis patients and divided the patients into three categories for stratified intervention [24]. Patients in each category were given an aerobic resistance exercise routine with the same content but a different frequency. Hill et al. and other research teams classified patients with low back pain into low, medium, and high-risk categories to enable stratified management. The stratified pattern greatly aided disease management [25]. It is important to note that these programs were designed to target a single disease. Different methods have been used to give patients the same intervention content at a different frequency, saving human resources and improving disease control. Thus, it is of great significance to explore the impact of stratified self-management on the outcomes of patients with DM-MCI.

Routine self-management often includes the use of offline educational materials such as health manuals and lectures. However, the Internet is not limited by space and time, which makes it an important tool for training and education. “Internet-assisted” medical treatment is being increasingly applied in nursing [26]. During the COVID-19 pandemic, this intervention has been used to optimize medical structures, dynamically monitor changes in patient conditions, and provide guidance for rapid rehabilitation [27]. Studies indicate that this has worked to effectively reduce the risk of viral spread and improve the efficiency of medical treatment [28]. Among numerous internet-assisted interventions, WeChat has become a commonly used social media software for Chinese researchers and patients, and many studies have adopted WeChat as a medium for internet-assisted self-management interventions, achieving positive results [29, 30]. It is worthwhile to evaluate the use of a stratified support pattern-based internet-assisted self-management therapy for DM-MCI with WeChat as the intervention medium. And randomized controlled trial (RCT), as an important method widely used in the clinical verification of intervention technology around the world, has been applied to the self-management research of more patients with mild cognitive impairment or diabetes patients [31]. Therefore, we will use RCT as the research design method to verify the effectiveness of stratified support pattern-based internet-assisted self-management therapy(SISMT) for DM-MCI.

The current study has designed a self-management intervention using the “Internet-assisted” stratified support-pattern may be able to consider the heterogeneity of patients more and provide them with more personalized intervention strategies. The aim is to use this approach to address the heterogeneous needs of patients with DM-MCI. Stratification was determined based on the cluster classification of patient cognitive function and self-management ability. Using these characteristics along with expert guidelines and consensus [32, 33], intervention measures will be implemented for a duration of 12 weeks. The effectiveness of the intervention on the self-management and cognitive function of each group of patients with DM-MCI will be explored.

### Study objectives and hypotheses

The primary objective of the study is to compare the effectiveness of a 12-week stratified support pattern-based internet-assisted self-management therapy(SISMT) and a health manual intervention mode(HMI) on the cognitive function of DM-MCI patients. The secondary objectives are to evaluate the effectiveness of the interventions on fasting blood glucose (FBG), HbA1c, Postprandial blood glucose (PBS) levels, depression, anxiety, quality of life, happiness, self-management ability, and diabetes health literacy.

The first primary hypothesis is that the cognitive function scores will show more improvement among participants in the SISMT group than those in the HMI group 12 weeks after the intervention. The secondary hypotheses are that participants in the SISMT group will have (1) better blood glucose control (FBS, HbA1c, PBS). (2) lower depression and anxiety scores, (3) higher quality of life and happiness scores, (4) improved self-management, and (5) better health literacy than those in the HMI group 12 weeks after the intervention.

### Theoretical framework

This study is based on the Knowledge to Action Cycle (KTA) framework developed by Graham et al. [34]. According to the KTA framework, knowledge to practice is a cyclic, dynamic, and complex process in which knowledge innovation and application are interlinked. The KTA includes seven steps, researchers participate in the entire research process, which this study will combine as follows: 1) Find problems and extract relevant knowledge to self-manage DM-MCI according to expert guidelines and consensus; 2) Consult with clinical experts about the operability of the intervention; 3) Assess patient needs and investigate the operability of using Wechat for older adults; 4) Implement the self-management stratified model in patients with DM-MCI; 5) Establish different reminder frequencies based on patient characteristics and review Wechat background data; 6) Measure outcome indicators and evaluate the intervention; 7) Provide feedback to the patients and urge them to continue the knowledge behavior transformation (Fig. 1).

**Fig. 1 Fig1:**
[figure not shown]
Theoretical framework of the study: the Knowledge to Action Cycle (KTA)

## Methods

### Trial design

This is a single-blind, two-arm randomized controlled trial with randomization at the participant level. Participants will be randomly allocated to receive a HMI (control) or a SISMT (intervention). Primary and secondary study outcomes will be collected for both groups at baseline (T0) and 12 weeks(T1), 24 weeks post-intervention(T2). As the study involves the older adults with MCIs, a few specific ethical procedures should be followed and ensured. Only those who signed the consent form can be included in this study, and a guardian as the legal representative should be asked to co-sign the consent form. The trial has been registered at ChiCTR.org.cn (ChiCTR2200061991, date:16/07/2022).

### Study aim, setting and ethics

To evaluate the effectiveness of a SISMT for DM-MCI will be conducted, with allocation concealment and outcome assessor blinding (Fig. 2).

**Fig. 2 Fig2:**
[figure not shown]
Flowchart of the SISMT for DM-MCI

### Participants

#### Recruitment and screening

By convenient sampling, patients with DM will be screened for MCI and included in the study. This study is approved by relevant hospital departments and most patients were recruited from the endocrine clinic at a provincial Third-Grade Class-A General Hospital. The study researchers will met with DM patients who were visiting the clinic and asked them to complete the Montreal Cognitive Assessment (MoCA) [35], the Mini-Mental State Examination (MMSE) [36], the diabetes self-management scale (DSCS) [37], and the Activity of Daily Living (ADL) survey [38], along with a general information questionnaire. The questionnaires will be completed in separate rooms of the hospital. So far, 240 DM-MCI patients have been screened.

#### Diagnosis criteria

MCI will be diagnosed using Petersen diagnostic criteria as follows [39]: 1) Chief complaint: memory decline; 2) MoCA score of 13–14 for illiteracy, 19–20 for patients with primary school education(1–6 years education), 24–25 for those with junior high school education(≥ 7 years education) [40]; 3) An MMSE score of 24–30 indicates the absence of dementia [41]. (4) ADL will be used to measure the intact activities of daily living (Lawton–Brody ADL score < 18) [38].

#### Inclusion criteria

1) Meet the diagnostic criteria for diabetes (The diagnosis of diabetes is based on the doctor's diagnosis results in the hospital diagnosis and treatment system). 2) Meet the diagnostic criteria for mild cognitive impairment. 3) ≥ 60 years of age. 4) No obvious visual or hearing impairments. 5) Participants have good communication skills and can cooperate with researchers to complete the survey questionnaire. 6) Able to use Internet device dependently.

